### Sample size

A power calculation was performed using the functional component of the WOMAC [18] as the primary outcome. Using the defined minimal clinically important difference in the WOMAC of 15 points [33], a standard deviation (SD) of 26.5, and an alpha 0.05 with a power of 80% to demonstrate a superior outcome in the intervention group (one tailed analysis), it was determined that 80 patients would need to be recruited (40 in each arm). Loss to follow-up data from other surgical arthroplasty studies in the institution with a similar follow-up regime were used to estimate a loss to follow-up of 10%. On this basis, 90 patients will be randomised to ensure the study achieves power.

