### Statistical analysis

Statistical analysis will be performed using Statistical Package for Social Sciences version 17.0 (SPSS Inc., Chicago, IL, USA). Parametric and non-parametric tests will be used as appropriate to assess continuous variables for significant differences between groups. Changes in key outcomes (WOMAC, OKS, EQ-5D) from baseline to 3, 6 and 12 months following surgery will be analysed using analysis of variance (ANOVA) and adjusted for multiple testing to compare the two intervention arms. The data is expected to demonstrate a normal distribution and this will be assessed prior to analysis. A *p*-value of <0.05 will be defined as significant for the primary outcome and a *p*-value of <0.01 will be defined as significant for the secondary outcomes to adjust for multiple testing.

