The final limitation was the use of the minimal clinically important difference of 15 points to power the study to the functional component of the WOMAC score. This was taken from Escoban et al. [33] whom defined the MCID to range from 15 to 22 points following TKR, and therefore, 15 points was taken as the lower limit and used to power the study. However, recently Clement et al. [34] have demonstrated the MCID may be as low as 9 points for the functional component of the WOMAC 1 year following TKR. Substituting this MCID of 15 for 9 and using a SD of 18 points (as observed by Clement et al. [34] for change in functional score) at least 102 patients would need to be recruited (51 in each treatment arm). Funding and study designed and infrastructure were all in place prior to the publication of this paper, and therefore, the study is continuing to aim to show a statistical 15 point or more difference, but it should be acknowledged a difference less than this may be non-significant but may be clinically significant if the difference is 9 points or more.

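### The sample size assumes a one-tailed test at 0.05, but the analysis section names an ANOVA at p<0.05, which is non-directional for two groups; used as written, power for 15 points is about 70%, not 80%

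*Protocol article*

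**What the plan says.** **Sample size.** The error rate, power and sidedness are set in these words: "an alpha 0.05 with a power of 80% to demonstrate a superior outcome in the intervention group (one tailed analysis"). The calculation concerns the functional component of the WOMAC, with a target difference of 15 points and an SD of 26.5. The result is 80 patients, 40 per arm, raised to 90 randomised for a 10% loss to follow-up.

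**Statistical analysis.** Continuous variables are tested for differences between the groups. Changes in the key outcomes, WOMAC among them, "will be analysed using analysis of variance (ANOVA) and adjusted for multiple testing to compare the two intervention arms". A p-value below 0.05 "will be defined as significant for the primary outcome", and below 0.01 for the secondary outcomes. The section mentions neither a one-tailed test nor a directional threshold.

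**Discussion.** For a smaller important difference of 9 points with an SD of 18, the article says "at least 102 patients would need to be recruited (51 in each treatment arm"). It does not state the sidedness of that figure.

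**Background and Trial design.** The null hypothesis is worded directionally (no improvement over manual surgery), and the trial is called a superiority trial.

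**The concern.** The size of the trial and the test of its primary outcome are both fixed in this article, and they rest on different tests at the same nominal 0.05. A one-tailed test puts the whole 5% on the side of benefit. The F test of a two-group ANOVA rejects for a difference in either direction, so only 2.5% falls on the side of benefit. A calculation made for the first test overstates the power of the second.

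Two things are at stake. First, the stated 80% does not describe the analysis as written. Second, some results would count as positive under one section and negative under the other. If that is unresolved when the data are seen, the more favourable test can be chosen afterwards. The Discussion accepts that patients are not blinded and that most outcomes are subjective and patient-reported, so a choice of this kind should not be left open.

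**Working it through.** **Inputs.** From Sample size: difference 15, SD 26.5, alpha 0.05, one-tailed, power 80%, 40 per arm, 10% loss, 90 randomised. From Statistical analysis: ANOVA, threshold 0.05. From Discussion: difference 9, SD 18, 51 per arm.

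**Method.** Two-sample t test with n per arm, df = 2n − 2, SE = SD × √(2/n) and noncentrality δ = difference / SE. Power is the probability that a noncentral t variable exceeds the critical value. The two-sided version uses the 97.5% point of t instead of the 95% point. For two groups F = t², so the ANOVA p-value is the two-sided t-test p-value.

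**Step 1: reproduce the plan.** At n = 40:
- SE = 26.5 × √(2/40) = 5.926
- δ = 15 / 5.926 = 2.531
- One-tailed critical t (78 df) = 1.665; power = 80.6%

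Forty per arm is the smallest n that reaches 80% one-tailed, so the stated 80 is right on its basis. For losses, 80 / 0.9 = 88.9, stated as 90.

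**Step 2: same inputs, ANOVA at p<0.05.** The two-sided critical t (78 df) is 1.991.

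| Quantity | One-tailed 0.05 | ANOVA at 0.05 (two-sided) |
|---|---|---|
| Power, 40 per arm | 80.6% | 70.5% |
| Power if all 90 are evaluable (45 per arm) | 84.6% | 75.7% |
| n per arm for 80% power | 40 | 50 |
| Difference detectable at 80% power, 40 per arm | 14.9 | 16.8 |

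Fifty per arm is 100 evaluable. With 10% loss, 100 / 0.9 = 111.1, so 112 randomised in equal arms. The allowance for losses therefore does not close the gap, even if nobody is lost.

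**Step 3: where the two sections give different answers.** The smallest significant observed difference, at 40 per arm and an observed SD of 26.5, is critical t × SE:
- one-tailed: 1.665 × 5.926 = 9.9 points
- ANOVA: 1.991 × 5.926 = 11.8 points

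A difference in favour of the intervention between these values is significant under one section and not under the other. The whole band lies above the 9 points that the Discussion says may be clinically significant.

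**Step 4: the figure in the Discussion.** For 9 points and SD 18, a one-tailed test needs 51 per arm (102), which reproduces the stated number. A two-sided test needs 64 per arm (128). The 102 therefore rests on the same one-tailed basis without saying so.

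**The case against.** The strongest reply is that the trial is meant to be one-tailed throughout. Sample size says so, the null in the Background is directional, and Trial design calls it a superiority trial. On that reading the 80% is correct, and the analysis section, condensed for a journal, merely fails to repeat the sidedness. Silence on sidedness could indeed be left to a fuller document. But the section is not merely silent: it names a procedure whose two-group p-value is non-directional and applies the 0.05 threshold to it. A directional hypothesis does not make an F test one-sided, and a superiority trial can use either kind of test.

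Three parts of the reply stand:
- A reader might infer that the protocol specifies a two-sided test. It never uses that term; two-sidedness is a property of the ANOVA it names.
- A reader might infer that the sample size was miscalculated. It was not: 80, 90 and 102 all follow from one-tailed inputs. This is an inconsistency between sections, not an arithmetic error.
- The 70.5% belongs to a simple comparison of change at 6 months. The analysis section also allows non-parametric tests and covers changes at 3, 6 and 12 months, and Sample size does not say whether 26.5 is the SD of the change or of the score. The analysis finally run could have different power.

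**Conclusion.** The point holds as an inconsistency on the primary outcome. The design claims 80% power from a one-tailed test, the written analysis is non-directional, and no section reconciles the two.

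If the ANOVA p-value is used as written, power for 15 points is about 70%, and about 76% even if all 90 patients are evaluable. The 70% assumes 80 evaluable patients split equally, an SD of 26.5 for the quantity analysed, an unadjusted comparison, and no multiplicity adjustment of the primary test beyond the stated 0.05.

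Two stronger readings are not supported. One is that the trial simply has 70% power: if a one-tailed 0.05 test is declared and used, the 80% stands, at the price of a 5% chance of falsely claiming benefit instead of 2.5%, and with no means of declaring a worse result in the robotic arm. The other is that adjusting for baseline would restore most or all of the lost power. The article gives no correlation between baseline and 6-month scores, so no amount of recovery can be claimed.

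**What to change.** Before analysis, state the sidedness of the primary test in Statistical analysis and bring Sample size and Discussion into line with it.

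- **Preferred:** keep the ANOVA as a two-sided test at 0.05. In Sample size, state that 80 evaluable patients give about 70% power for 15 points at SD 26.5, and 80% power for 16.8 points. In Discussion, replace 102 with 128 evaluable (64 per arm). Do not enrol more patients on this account.
- **If the one-tailed test is kept:** say so in Statistical analysis, give its 5% one-sided error, and name a test that yields a one-sided p-value. In Discussion, label 102 as one-tailed.

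In neither case should the text promise that baseline adjustment recovers the power.

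The cost is a few sentences and, under the preferred option, a less favourable stated power. No patients, visits or data are added.

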### Data recording and record keeping

Data will be collected by the site researcher (baseline collection), clinicians delivering the interventions and participants (health utility and assessment questionnaires). All data requested on the CRF must be recorded. All missing data must be explained. If a space on the CRF is left blank because the procedure was not done or the question was not asked ‘N/D’ will be written. If the item is not applicable to the individual case, ‘N/A’ will be written. If the data item is unknown, ‘NK’ will be written. If a data item has not been recorded on source data then ‘NR’ will be written. All entries should be printed legibly in black ink. If any entry error has been made, to correct such an error, a single straight line should be drawn through the incorrect entry and the correct data entered above it. All such changes must be initialled and dated and errors should not be erased or whited out. For clarification of illegible or uncertain entries, the clarification should be printed above the item, then initialled and dated.

All trial data will be entered on to paper CRFs and subsequently inputted into the trial database by the research team. In accordance with the ICH GCP (Section 5.5) [61], electronic data entry systems will be validated and standard operating procedures for data entry will be maintained.

The study will be conducted in accordance with the current approved protocol, ICH GCP, relevant regulations and standard operating procedures. Regular monitoring will be performed according to ICH GCP. Data will be evaluated for compliance with the protocol and accuracy in relation to source documents. Following written standard operating procedures, the monitors will verify that the clinical trial is conducted, and data are generated, documented and reported in compliance with the protocol, GCP and the applicable regulatory requirements. Monitoring and auditing will be undertaken in accordance with the sponsors policies and procedures and complying with Department of health Research Governance Framework for Health and social care (2005).

The chief Investigator and other key staff will attend site initiation training, coordinated by the research team, which will incorporate elements of trial-specific training necessary to fulfil the requirements of the protocol. Training will consist of reviewing the trial protocol, recruitment, consent, randomisation, follow-up, trial procedures, intervention training as applicable, trial arrangements, data protection and data handling.

## Dissemination policy

The results of the study will be presented at local, national and international meetings. Publication of the study will likely take part in several stages with the main focus being the primary outcome. However, we suspect there will be too much data to present in one encompassing manuscript and several publications relating to the secondary outcomes will be published.

## Discussion

This study aims to assess whether the improved accuracy of implant alignment using robotic arm-assisted surgery and the Verasense^TM^ (OrthoSensor Inc. Dania Beach, FL, USA) aids the surgeon to balance the TKR intraoperatively results in a greater improvement in the early knee-specific outcome. In addition, the secondary outcomes assessed in this study will enable quantification of the patient’s expectations fulfilment, improvement in their general health, restoration normal gait and patient satisfaction. Furthermore, the study aims to assess whether robotic arm-assisted TKR is a cost-economically viable treatment within the National Health Service in the UK.

The major limitation of the study design is the non-blinding of the patients to the intervention that they will receive, and this may bias the patient-reported outcomes measures assessed. The reason for this is due to the need for a pre-operative CT scan in those patients randomised to undergo robotic arm-assisted TKR and associated radiation exposure; therefore, patients needed to be informed of this prior to enrolling to the study. The authors considered performing placebo CT scans for those undergoing manual TKR using jig-based systems to enable blinding of the patients, but this was not possible due to the fact patients would be exposed to a significant dose of radiation that would be of no benefit to the patient. The assessors were blinded to the intervention arm, but the majority of the outcome measures assessed in this study are subjective patient reported outcomes.

The final limitation was the use of the minimal clinically important difference of 15 points to power the study to the functional component of the WOMAC score. This was taken from Escoban et al. [33] whom defined the MCID to range from 15 to 22 points following TKR, and therefore, 15 points was taken as the lower limit and used to power the study. However, recently Clement et al. [34] have demonstrated the MCID may be as low as 9 points for the functional component of the WOMAC 1 year following TKR. Substituting this MCID of 15 for 9 and using a SD of 18 points (as observed by Clement et al. [34] for change in functional score) at least 102 patients would need to be recruited (51 in each treatment arm). Funding and study designed and infrastructure were all in place prior to the publication of this paper, and therefore, the study is continuing to aim to show a statistical 15 point or more difference, but it should be acknowledged a difference less than this may be non-significant but may be clinically significant if the difference is 9 points or more.

## Trial status

Protocol version 1.0 date 13/12/2018. Patient recruitment date: May 2019. Estimated completion of recruitment date: May 2021. Estimated completion of final follow-up date: December 2022.

## Data Availability

The datasets used and/or analysed during the current study are available from the corresponding author on reasonable request.

## Abbreviations

AE: Adverse event
ADE: Adverse device effect
CI: Chief Investigator
CRF: Case report form
CRO: Contract Research Organisation
CT: Clinical trials
CT scan: Computed tomography scan
CTA: Clinical Trials Authorisation
EC: Ethics Committee (see REC)
FJS: Forgotten Joint Score
GCP: Good Clinical Practice
GP: General Practitioner
ICF: Informed Consent Form
ICH: International Conference of Harmonisation
IEC: Independent Ethics Committee
IRB: Independent Review Board
MHRA: Medicines and Healthcare products Regulatory Agency
NHS: National Health Service
NRES: National Research Ethics Service (previously known COREC)
OA: Osteoarthritis
OKS: Oxford knee score
PI: Principal Investigator
PIL: Participant/ Patient Information Leaflet
R&D: NHS Trust R&D Department
REC: Research Ethics Committee
SAE: Serious adverse event
SADE: Serious adverse device effect
SIL: Subject Information Leaflet (see PIL)
SOP: Standard operating procedure
TKR: Total knee replacement
TMF: Trial Master File
UADE: Unanticipated adverse device effect
WOMAC: Western Ontario and McMaster Universities Osteoarthritis
